### Intervention

2.6

Patients in these three groups are required to receive conventional therapy and rehabilitation training recommended by the Stroke Prevention and Treatment Guideline 2024 (SPTG 2024) (17). Acupuncture treatment will be performed by acupuncturists who hold a Chinese medicine practice license issued by the National Health Commission of the People’s Republic of China and have 5 years of acupuncture clinical experience. Locations of acupoints are displayed in Table 2 and Figure 2.

**Table 2 tab2:** Acupuncture point locations.

Acupoints	Location
GV20 (Baihui)	On the head, 5 cun directly above the midpoint of the anterior hairline at the midpoint of the line connecting the apexes of both ears.
GV24 (Shenting)	On the head, 0.5 cun directly above the midpoint of the anterior hairline.
EX-HN1 (Sishencong)	On the vertex of the head, 1 cun anterior, posterior, and lateral to Baihui (GV20).
LI10 (Shousanli)	On the radial side of the dorsal surface of the forearm and on the line connecting Yangxi (LI5) and Quchi (LI11), 2 cun below the cubital crease.
LI11 (Quchi)	On the lateral aspect of the elbow, at the midpoint of the line connecting LU5 with the lateral epicondyle of the humerus.
LI15 (Jianyu)	On the shoulder, superior to the deltoid muscle, in the depression anterior and inferior to the acromion when the arm is abducted or raised to the shoulder level.
TE5 (Waiguan)	On the posterior aspect of the forearm, 2 cun proximal to the dorsal wrist crease at the midpoint between the ulna and radius.
ST36 (Zusanli)	3 cun directly below Dubi (ST35) in the depression, one fingerbreadth lateral to the anterior crest of the tibia.
GB34 (Yanglingquan)	In the depression anterior and inferior to the head of the fibula at the tibiofibular articulation.
GB39 (Xuanzhong)	On the lateral side of the leg, 3 cun above the tip of the external malleolus on the anterior border of the fibula.

**Figure 2 fig2:**
[figure not shown]
Locations of acupoints.

#### Acupuncture group

2.6.1

The treatment plan will be developed based on previous literature (18) and consensus among acupuncture experts. The following acupoints will be selected: Baihui (GV20), Shenting (GV24), Sishencong (EX-HN1), Jianyu (LI15), Quchi (LI11), Shousanli (LI10), Waiguan (TE5), Yanglingquan (GB34), Zusanli (ST36), and Xuanzhong (GB39). The head and impaired limb will be exposed, and the skin at the acupoints will be disinfected with 75% alcohol, and 3 M adhesive plastic pads will be applied to the acupoints. These acupoints will be punctured with disposable stainless steel needles (0.25 mm × 40 mm, Andi) into the subcutaneous tissue or the galea aponeurotica of the head through these pads. The procedure will be as follows: Baihui (GV20), Shenting (GV24), and Sishencong (EX-HN1) will be punctured to a depth of 0.5–1 cun (a cun is a traditional Chinese proportional body-based unit used in acupuncture) at an angle of 15–30°, and the needles will then be manipulated by twisting for 2 min at a frequency of 200 twists/min. For Jianyu (LI15), Quchi (LI11), and Yanglingquan (GB34)—located around the shoulder, elbow, and knee joints, respectively—the needles will be punctured perpendicularly at a depth of 1–1.5 cun to achieve deqi (sensation of soreness, distension, and heaviness); then the needles will be withdrawn to the subcutaneous layer. Subsequently, the needles will be redirected and punctured obliquely to a depth of 1 cun, and the acupuncturist will assist patients in performing slow movements of the shoulder, elbow, and knee joints to gradually relieve spasticity. The other acupoints will be punctured perpendicularly to a depth of 1 cun and manipulated using lifting, thrusting, and rotating to facilitate deqi. Each treatment session will last 25–30 min, and during the needle retention period, the needles will be manipulated by lifting, thrusting, twirling, and rotating every 10 min to maintain the deqi sensation. Each participant will receive 12 sessions of acupuncture treatment (three times per week).

#### Sham acupuncture group

2.6.2

Participants assigned to this group will receive non-penetrating sham acupuncture at the same acupoints as the acupuncture group. The blunt-tip retractable needle (0.25 mm × 40 mm) was fixed on the acupoint through a 3 M adhesive plastic pad. When the acupuncturist pressed the needle, the blunt tip contacted the skin without penetrating it, producing only a pricking sensation. Simultaneously, the needle body retracted into the handle, creating the “visual mimicry” of penetration. Participants in this group will undergo the same needle manipulation, treatment frequency, and duration as those in the acupuncture group. The needles used in the sham group were identical in appearance, material, and size to the real ones, and the 3 M plastic pads were matched in shape, color, and application method.

#### Basic treatment group

2.6.3

Participants will not receive acupuncture treatment in this group but will only receive conventional therapy and rehabilitation training recommended by the Stroke Prevention and Treatment Guideline 2024 (SPTG 2024). Patients in this group who complete follow-up are eligible for a complimentary 4-week (12 sessions) acupuncture treatment.

### Outcome measurements

2.7

#### Primary outcome

2.7.1

In this trial, the primary outcome will be defined as the change in Modified Ashworth Scale (MAS) scores from baseline to week 4 of treatment. The MAS is a validated clinical tool used to assess the severity of muscle spasticity and evaluate treatment efficacy (19, 20). It comprises six ordinal grades—0, I, I+, II, III, and IV—which correspond to numerical scores of 0, 1, 2, 3, 4, and 5, respectively. Higher grades and scores indicate greater spasticity severity. In this study, MAS assessments will be conducted bilaterally on the biceps brachii and tibialis anterior muscles of patients with PSS.

#### Secondary outcomes

2.7.2

##### Fugl-Meyer assessment

2.7.2.1

The Fugl-Meyer Assessment (FMA) is a standardized and validated tool widely used to comprehensively evaluate motor impairment following neurological injury (21). The FMA includes five dimensions (motor function, sensation, balance, range of motion, and joint pain). The upper limb score ranges from 0 to 66, with the lower limb score ranging from 0 to 34; the more severe the symptoms, the lower the score.

##### Clinical spasticity index

2.7.2.2

The Clinical Spasticity Index (CSI) is used for the quantitative assessment of muscle spasticity. CSI includes tendon reflexes, muscle tone, and clonus, with a score ranging from 0 to 16, in which 0–9 indicates mild spasticity, 10–12 indicates moderate spasticity, and 13–16 indicates severe spasticity.

##### National Institutes of Health Stroke Scale

2.7.2.3

The National Institutes of Health Stroke Scale (NIHSS) is used to assess the severity of neurological impairment in patients with stroke, to evaluate prognosis, and to monitor disease progression. It consists of 11 items with total scores ranging from 0 to 42, in which 0–1 means normal or nearly normal, 1–4 means minor stroke, 5–15 means moderate stroke, 15–20 means moderate to severe stroke, and 21–42 means severe stroke.

##### Modified Barthel Index

2.7.2.4

The Modified Barthel Index (MBI) is commonly used to assess activities of daily living (22). It has 10 items covering feeding, bathing, dressing, grooming, transferring, and other factors, with a total score of 100. Higher MBI scores indicate a higher quality of life.

##### Surface electromyography

2.7.2.5

Surface electromyography (sEMG) is an important indicator to evaluate neuromuscular activity under static and dynamic states, with the advantages of being non-invasive, real-time, and capable of multi-target measurement (23). Studies have indicated that changes in sEMG parameters correlate with limb dysfunction (assessed by FMA) and spasticity (assessed by MAS) (24). Integrated electromyography (IEMG), median frequency (MF), and root mean square (RMS) will be used as indicators for efficacy evaluation in this study.

##### Shear-wave ultrasound elastography

2.7.2.6

Shear-wave ultrasound elastography (SWUE) is used to quantitatively assess the mechanical properties of muscles, such as stiffness, elasticity, and changes in echogenicity. It is helpful to judge the definitive diagnosis and effectiveness of treatment (25, 26). The maximum modulus values (Emax) will be measured and evaluated before and after the treatment in this trial.

In this study, the FMA, CSI, NIHSS, and MBI scores will be assessed at baseline, 2 weeks, 4 weeks, and during follow-up. MAS, sEMG, and SWUE will be evaluated at baseline and 4 weeks. The integration of MAS and CSI with sEMG and SWUE enables a comprehensive assessment of spasticity severity, muscle electrophysiological activity, and morphological characteristics (e.g., muscle fiber thickness and echo intensity). Meanwhile, the FMA, NIHSS, and MBI collectively focused on evaluating improvements in neurological function and the enhancement of real-world quality of life.

### Safety and adverse events

2.8

The acupoints selected in this trial are based on a consensus among acupuncture experts and are considered relatively safe. Potential adverse events included pain, numbness, subcutaneous swelling, bruising, fainting during acupuncture, needle sticking, or needle bending. If an adverse event occurs, it will be recorded in detail in the Case Report Forms (CRFs). Serious adverse events, such as syncope, deep tissue infection, or abscess, will be promptly reported to the Ethics Committee, and affected participants will be immediately withdrawn from the trial and provided with active and effective treatment.

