### Quality control and data management

2.10

Outcome assessors will collect all participant data using paper-based CRFs and subsequently enter the data into an electronic database. The research team will conduct periodic data monitoring to verify completeness, accuracy, and authenticity while concurrently tracking trial progress and adherence to the intervention protocol. To enhance adherence, researchers will maintain regular contact with the participants via telephone or WeChat, providing reminders to actively engage in treatment, scheduled assessments, and follow-up visits. All adverse events and reasons for participant discontinuation—whether from the trial or from follow-up—will be systematically documented.

Acupuncturists, outcome assessors, and statisticians will all receive standardized training on the study protocol to ensure a full understanding of the study procedures and details. Specifically, acupuncturists will complete comprehensive professional training covering acupoint selection and localization, acupuncture techniques, treatment frequency and duration, and distinct protocols for both verum and sham acupuncture, thereby ensuring intervention consistency and fidelity across all participants. All members of the research team will attend scheduled organizational meetings every three weeks to review the progress, identify challenges, and collaboratively resolve issues arising during the trial.

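### Section 2.8 names fainting among potential adverse events and syncope among serious ones, with different consequences and nothing to separate them

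*Protocol article*

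**What the plan says.** Everything that bears on the point stands in four consecutive sentences of section 2.8 (Safety and adverse events) and in short remarks elsewhere.

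- After an opening sentence on the choice of acupoints, the section lists what is expected: "Potential adverse events included pain, numbness, subcutaneous swelling, bruising, fainting during acupuncture, needle sticking, or needle bending".
- The next sentence gives the general handling: "If an adverse event occurs, it will be recorded in detail in the Case Report Forms (CRFs". No other action is attached to adverse events as a class.
- The last sentence turns to serious events: "Serious adverse events, such as syncope, deep tissue infection, or abscess, will be promptly reported to the Ethics Committee". It continues: "affected participants will be immediately withdrawn from the trial and provided with active and effective treatment".
- Section 2.10 (Quality control and data management) says of "All adverse events and reasons for participant discontinuation" only that they will be documented. Section 2.4 (Patient adherence) says much the same of adverse events and dropouts.

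**The concern.** A patient who faints on the treatment table and soon recovers fits the fainting entry in the first list. Many clinicians would also call the event syncope, the first example in the serious-event sentence. The two entries lead to different consequences: a form entry alone, or a form entry plus an ethics report plus removal from the trial.

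Three things then depend on a reading that the text does not settle: how many serious events are counted, which events the Ethics Committee hears of, and who stays in the trial. Safety is one of the stated aims (Abstract and end of the Introduction). Withdrawal also touches efficacy, because section 2.12 analyses all randomised participants and fills missing values by multiple imputation. A participant removed before week 4 may therefore contribute an imputed primary outcome.

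**Working it through.** The plan gives no figure to reproduce. The check is a comparison of the texts.

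**Side by side (section 2.8)**

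| | Fainting entry | Syncope entry |
|---|---|---|
| Heading of the list | Potential adverse events | Serious adverse events |
| Neighbouring entries | Pain, bruising, needle sticking, needle bending | Deep tissue infection, abscess |
| Setting | Tied to acupuncture | Not tied to a session or an arm |
| Recording in the form | Yes | Yes, as an adverse event |
| Prompt ethics report | Not stated | Yes |
| Immediate withdrawal | Not stated | Yes |
| Qualifier by severity, duration or outcome | None | None |

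**Is there a rule that separates them?** Sections 2.4, 2.8 and 2.10 are the places where adverse-event handling is described. None of them, nor any other part of the article, gives a seriousness criterion, a grade or a definition that separates the two terms.

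**What each reading implies for a faint during a session**

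1. The terms mean the same. The sentences then add up: the faint is recorded, reported, and the participant withdrawn. Recording alone would breach the last sentence.
2. The terms differ, for example fainting as a milder needling reaction and syncope as something graver. Some faints are then recorded only. The article does not say which.

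Both readings are open on the text.

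**Size, as illustration only.** The article gives no fainting rate. Suppose a proportion *p* of participants faints at least once over the 12 sessions. For one arm of 60, P(at least one) = 1 − (1 − *p*)^60. For the two session arms together, the expected number is 120 × *p*.

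| Assumed *p* | P(at least one in 60) | Expected in 120 |
|---|---|---|
| 1% | 1 − 0.99^60 = 0.453 | 1.2 |
| 2% | 1 − 0.98^60 = 0.702 | 2.4 |
| 5% | 1 − 0.95^60 = 0.954 | 6.0 |

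Suppose three acupuncture patients faint and nothing else serious occurs. If all three count as syncope, the serious-event proportion is 3/60 = 5%, and three participants are withdrawn. If none does, it is 0/60 = 0%, and none is withdrawn on this ground. Section 2.11 allows for the loss of 60 − 48 = 12 per arm, so three withdrawals would use a quarter of that allowance (3/12).

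**The case against.** The strongest reply is that serious events are a subset of adverse events, so a term may properly belong to both lists. Section 2.8 never labels the first list non-serious, and its instructions are cumulative. This stands, and it rules out calling the section self-contradictory. A reader might infer that a site could follow either sentence and comply. That does not hold if the two terms mean the same event; it holds only if they can be read as different events.

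Second, the first list ties fainting to needling, while syncope stands beside deep infection and abscess, so a graded distinction may be intended. That is possible, but the article does not state it. A subset needs a rule for membership, and none is given.

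Third, a journal article may leave seriousness definitions to the full protocol. This also stands: a missing definition alone would be no finding, and the phrase introducing the serious events marks them as examples, not as a definition. But the article chose to name events and attach consequences to them, and those names overlap. The point rests on that stated text.

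Fourth, the trial has one centre, with standardised training and regular team meetings (sections 2.1 and 2.10). These may reduce inconsistency in practice, but they do not tell staff which reading to be trained on.

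**Conclusion.** The point holds as an unresolved overlap. Section 2.8 attaches different consequences to two terms that overlap in ordinary use and gives nothing to separate them. Safety counts, ethics reports and withdrawals can therefore be inconsistent from patient to patient.

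Its size cannot be fixed from the document. The percentages rest on assumed fainting rates, and the range of 0% to 5% rests on an assumed three faints. The primary outcome's definition, the sample-size calculation and the planned tests are not affected.

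Two further inferences are not supported:

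- That only patients having sessions can be affected. Fainting during acupuncture can arise only in the two session arms over the four treatment weeks, but syncope as worded in 2.8 could occur in any arm. Hence mainly, not only, those two arms.
- That the serious-event rate is the trial's key safety figure. No section names it as an outcome or specifies an analysis of it.

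**What to change.** Reconcile the two sentences of section 2.8:

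- Record every faint or syncope under one term, with a severity grade, in all three arms.
- State one seriousness criterion, applied equally to all arms, that decides whether such an event is also serious.
- Make the reporting and withdrawal consequences follow from that one classification, so that like events are handled alike.

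Which classification, reporting and withdrawal action applies is for the sponsor and Ethics Committee to decide; nothing here favours one. If fainting during acupuncture was meant as a milder reaction distinct from syncope, saying so explicitly would be part of the same edit.

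The cost is a change of wording in 2.8 and one field on the adverse-event form. The number of events counted as serious may change as a result.

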### Statistical analyses

2.12

All statistical analyses will be performed using IBM SPSS Statistics 25.0. Intention-to-treat (ITT) analysis will be applied to all randomized participants, with missing data handled through multiple imputation methods. Normality tests will be conducted on all data, and continuous variables with a normal distribution will be presented as the mean±SD. Otherwise, the data will be expressed as M (P25-P75). For comparisons among the three groups, continuous variables will be analyzed using parametric tests (ANOVA) or non-parametric tests (Kruskal-Wallis) based on the data features. Categorical variables will be compared using the chi-square test. A *p* value of <0.05 will be defined as statistically significant. Efficacy analyses will be performed on both intention-to-treat (ITT) and per-protocol (PP) populations, with the ITT set including all randomized participants analyzed according to their allocated groups, regardless of protocol deviations, whereas the PP set will consist of participants who comply with the trial procedures without major deviations.

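### Section 2.8 takes participants with a serious adverse event out of the trial, not only off treatment, so their week-4 MAS is avoidably lost and must be imputed in the ITT analysis

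*Protocol article*

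**What the plan says.** Section 2.8 (Safety and adverse events) sets the rule. The trigger is "Serious adverse events, such as syncope, deep tissue infection, or abscess", and the consequence, besides a report to the Ethics Committee, is that "affected participants will be immediately withdrawn from the trial and provided with active and effective treatment". The rule is not restricted to any arm. The same section's list of ordinary potential adverse events includes "fainting during acupuncture, needle sticking, or needle bending".

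Section 2.12 (Statistical analyses) states: "Intention-to-treat (ITT) analysis will be applied to all randomized participants, with missing data handled through multiple imputation methods". It defines the efficacy populations "with the ITT set including all randomized participants analyzed according to their allocated groups, regardless of protocol deviations", and adds a per-protocol set. It does not describe the imputation model.

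Section 2.10 (Quality control and data management) has the reasons for discontinuation documented, "whether from the trial or from follow-up". It does not say that a participant who discontinues is still assessed.

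Section 2.7.1 puts the primary endpoint at week 4, the end of the treatment period. Table 1 schedules adverse-event recording in weeks 1 to 4.

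**The concern.** Stopping study treatment and stopping outcome collection are separate decisions, and an ITT analysis depends on keeping them separate. Section 2.8 merges them. Adverse events are recorded during the four treatment weeks and the primary endpoint falls at the end of those weeks, so following the rule usually means that the primary MAS is not observed.

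The protocol itself creates this loss, for a reason linked to treatment. Multiple imputation as usually run assumes that data are missing at random given what was observed, and section 2.12 names no other assumption. If participants with a serious event do worse than the imputation predicts, their arm looks better than it should.

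The loss may also differ by arm. The rule covers all three arms. However, deep infection or abscess from needling is plausible mainly with real acupuncture: the sham needle does not penetrate the skin (section 2.6.2) and the basic treatment group is not needled during the comparison (section 2.6.3). Syncope could occur in either arm that has a needling procedure.

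A statistical analysis plan cannot recover outcomes that the protocol stops collecting. The trial also aims to assess safety, so these are participants whose course it should want to observe.

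**Working it through.** **1. The plan's own figure.** Section 2.11 needs 48 evaluable participants per group and allows 20% dropout: 48 / (1 − 0.20) = 60 per group, 180 in total. This reproduces exactly. It leaves room for 60 − 48 = 12 losses per group. That allowance protects precision; it does not protect against bias when the losses are related to outcome.

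**2. Inputs for the size of the bias.**
- From section 2.11: predicted mean MAS reductions of 2.58 (acupuncture), 1.00 (sham) and 2.19 (basic), with SDs of 1.36, 1.62 and 1.48.
- Planned differences: 2.58 − 2.19 = 0.39 (acupuncture minus basic) and 2.58 − 1.00 = 1.58 (acupuncture minus sham).
- Assumed, because the article gives neither: *w*, the number of acupuncture participants withdrawn (1 to 3 of 60), and *g*, the amount by which their true MAS reduction falls short of the imputed value.
- Range for *g*: the low end, 0.39, applies if they are imputed at 2.58 but truly improve as the basic group does. The high end, 1.58, applies if they truly improve only as the sham group does.

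**3. Formula.** Overstatement of the acupuncture mean = (*w* / 60) × *g*.

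| *w* | *g* | Overstatement | Share of 0.39 | Share of 1.58 |
|---|---|---|---|---|
| 1 | 0.39 | 0.0065 | 1.7% | 0.4% |
| 3 | 0.39 | 0.0195 | 5.0% | 1.2% |
| 1 | 1.58 | 0.026 | 6.8% | 1.7% |
| 3 | 1.58 | 0.079 | 20.3% | 5.0% |

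**4. Against sampling error.** With 60 per arm, the SE of acupuncture minus sham is √[(1.36² + 1.62²) / 60] = √(4.474 / 60) = 0.27. The largest value in the table is 0.079 / 0.27, about 0.3 SE; the smallest is about 0.02 SE.

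**5. An outer case.** If all 12 allowed losses in the acupuncture arm were of this kind with *g* = 1, the overstatement would be (12 / 60) × 1 = 0.20, which is 51% of 0.39 and 13% of 1.58. Nothing in the article suggests that many serious events.

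**6. Who is withdrawn.** Section 2.8 lists fainting during needling among ordinary potential events and syncope among serious ones. As written, the same episode could be simply recorded or could end participation. The value of *w* therefore depends partly on a classification that the section leaves unclear.

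**The case against.** The strongest reply has four parts.

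*There is no contradiction.* A reader might infer that section 2.8 contradicts the ITT commitment, or makes the analysis ITT in name only. The text does not support that. "the ITT set including all randomized participants analyzed according to their allocated groups, regardless of protocol deviations" still covers a withdrawn participant, and the gap is dealt with "with missing data handled through multiple imputation methods". This part stands: the rule weakens the ITT analysis but does not contradict it.

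*The imputation model is unknown.* A reader might assume that missing values will be drawn from unaffected participants in the same arm. Section 2.12 does not say so, and such detail commonly sits in an analysis plan that is not shown. FMA, CSI, NIHSS and MBI are scheduled at week 2 and could inform the imputation. This also stands, so the sizes above are illustrative. An event before week 2, however, leaves no scheduled post-baseline assessment to draw on.

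*The direction is not fixed.* A reader might infer that the bias always favours acupuncture. Serious events in the sham or basic group trigger the same withdrawal and could push the other way. Nothing in the article shows that syncope or an abscess predicts a worse week-4 MAS. This stands: the bias could favour acupuncture, under a stated condition.

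*A condensed article may omit retention procedures.* Section 2.10 does separate leaving the trial from leaving follow-up. But section 2.8 is not silent: it states a rule, and the rule is withdrawal from the trial. Even if that means only the treatment phase, the primary endpoint falls at the end of that phase. If only treatment discontinuation is intended, the sentence says something else. This part does not remove the point.

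**Conclusion.** The point holds as an avoidable loss of primary outcome data, created by a stated rule. Participants with a serious adverse event leave the trial, no section keeps them in outcome assessment, and they reach the ITT analysis through imputation.

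The likely effect is small: about 0.007 to 0.08 MAS points on the acupuncture mean, or about 2% to 20% of the 0.39 difference from basic treatment and at most 5% of the 1.58 difference from sham. A reader might take the 7% and 20% figures alone as the size of the problem. They apply only if withdrawn participants improve no more than the sham mean; with the basic-group mean the figures are 1.7% and 5%.

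The range rests on 1 to 3 withdrawals, on imputation near the acupuncture mean, and on a shortfall between 0.39 and 1.58, none of which the article gives. The case for a change rests on the loss being avoidable, possibly informative and irrecoverable, not on a large expected bias.

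**What to change.** In section 2.8, separate stopping study treatment from leaving the trial. Leave the treatment decision to the clinical team as already defined. State that participants with a serious adverse event continue the scheduled MAS and other assessments unless they withdraw consent, that they are analysed in their allocated group, and that only data still missing are imputed. Carry the same distinction into the CRF instructions.

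Reconcile the entries for fainting and syncope in section 2.8, because they determine who falls under the rule. No view is taken here on how either should be classed or managed.

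The cost is a short change of wording and slight extra effort to follow these participants at visits already in Table 1. The sample size stays at 60 per group and no treatment decision changes.
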